# Sample Size

(ICH E3; 9.7.2. ICH E9; 3.5)

The sample size for the study was determined to be 150 participants based on a prior study [2], which measured EEG activity in adult males to investigate the therapeutic effects of NF training.

# General Considerations

## Timing of Analyses

The final analysis will be conducted after all participants have completed the study protocol, including the follow-up assessments on Day 4.

## Analysis Populations

(ICH E3; 9.7.1, 11.4.2.5. ICH E9; 5.2)

### Full Analysis Population

- All participants who completed the learning phase and provided at least one valid METEOR score or Gist score during the testing phases (Day 1, Day 2, Day 4).

### Per Protocol Population

- Successfully completed the gaming intervention and all post-gaming assessments without protocol deviations.

### Safety Population

- All participants who completed the learning phase participated in the gaming intervention (Day 1).
- Participants monitored for adverse events during or after the gaming phase (e.g., discomfort with EEG equipment).

## Covariates and Subgroups

(ICH E3; 9.7.1, 11.4.2.1. ICH E9; 5.7)

**1. Covariates**

The following covariates will be included in the analysis, particularly for difference in differences (DID) analysis conducted for secondary outcome:

- **Feedback Cycle Times:** The time taken during the learning phase will be analyzed to control for learning efficiency as a potential confounding factor.
- **Frequency of Image Repetition:** The number of times participants repeatedly viewed images during the learning phase analyzed as a measure of potential confounding factor on memory performance.

**2. Subgroups**

Subgroup analyses will be conducted to evaluate the interaction effects between the following variables:

- **Exposure Condition:**
  - Control, Conscious, Unconscious.
- **Emotional Valence:**
  - Positive, Negative.

**3. A Priori Hypotheses**

- **Hypothesis:** On Day 1, participants will exhibit lower METEOR and Gist scores for images cued through conscious or unconscious exposure compared to images in the control condition.

## Missing Data

(ICH E3; 9.7.1, 11.4.2.2. ICH E9;5.3. EMA Guideline on Missing Data in Confirmatory Clinical Trials)

Missing data will be quantified as a percentage for each variable, including METEOR scores, Gist scores, and EEG epochs.

- **Patterns of Missingness:** Missing data will be categorized as permanent, transient, or monotonous to identify potential causes.
- **Handling Missing Data:**
  - Missing METEOR and Gist scores will not be imputed; analyses will use available data (complete case analysis).
  - Missing EEG epochs due to artifacts will be excluded from analysis.

## Interim Analyses and Data Monitoring

(ICH E3; 9.7.1, 11.4.2.3. ICH E9; 4.1, FDA Feb 2010 “Guidance for Industry Adaptive Design Clinical Trials for Drugs and Biologics”)

No interim analyses or formal data monitoring procedures are planned for this study. The study will proceed as designed without modifications based on interim data reviews.

# Summary of Study Data

All continuous variables will be summarized using the following descriptive statistics: n (non-missing sample size), mean, standard deviation, median, maximum and minimum. The frequency and percentages (based on the non-missing sample size) of observed levels will be reported for all categorical measures. In general, all data will be listed, sorted by treatment and subject, and when appropriate by visit number within subject. All summary tables will be structured with a column for each treatment in the order (Control, Treatment) and will be annotated with the total population size relevant to that table/treatment, including any missing observations.

## Subject Disposition

**Study Stages and Participation:**

- Number of participants screened.
- Number of participants who completed the learning phase (Day 1).
- Number of participants who completed the gaming phase (Day 1).
- Number of participants who completed follow-up assessments on Day 2 (24 hours post-gaming) and Day 4 (72 hours post-gaming).
- Number of participants who dropped out, with reasons categorized as follows:
- Withdrawal of consent.
- Technical issues (e.g., EEG recording failure).
- Failure to adhere to protocol (e.g., excessive feedback cycle time deviations).

The summary statistics will be produced in accordance with section 9.

## Protocol Deviations

**1. Definition of Major Deviations**

Major deviations are defined as those that significantly affect the integrity of the data or the primary and secondary outcomes. Examples include:

- Participants whose feedback cycle times during the learning phase fall outside the interquartile range (IQR), indicating abnormal or inconsistent learning performance.
- Participants with significant EEG recording issues (e.g., excessive artifacts, technical failure) that result in unusable EEG data.
- Participants who failed to complete the gaming phase or any of the required assessments on Day 1, Day 2, or Day 4.

**2. Impact on Analysis Populations**

- **Full Analysis Population (FAP):**
  - Participants with minor deviations (e.g., small timing discrepancies) will remain included.
  - Major deviations will not exclude participants from the Full Analysis Population.
- **Per Protocol Population (PPP):**
  - Participants with major protocol deviations (e.g., unusable EEG data, extreme feedback cycle outliers) will be excluded.

The summary statistics will be produced in accordance with section 9.

## Demographic and Baseline Variables

As this study employs a within-subject design, detailed baseline comparisons between groups are not required. Only the following demographic variables will be recorded and summarized: Age, Gender, Corrected Visual Acuity (Binocular average)

The summary statistics for these variables will be produced in accordance with Section 9 of this SAP.

## Concurrent Illnesses and Medical Conditions

There are no concurrent illnesses or medical conditions recorded for this study, as they are not relevant to the study design or analysis.

## Prior and Concurrent Medications

No prior or concurrent medications were recorded in this study, as they are not relevant to the study design or outcomes.

## Treatment Compliance

In this study, treatment compliance will be evaluated to determine how well participants adhered to the experimental procedures. Since the study relies on experimental tools such as the gaming intervention and EEG recordings, compliance will be assessed based on two main criteria. First, usage records will be used to track the time participants spent engaging with the gaming intervention during the experimental phase. Second, the quality of EEG data will be considered, specifically focusing on the number of valid EEG epochs collected during the gaming session. These measures reflect the participants’ adherence to the study protocol and the reliability of the data collected.

# Efficacy Analyses

The efficacy variables in this study will be summarized to evaluate the effects of exposure condition (Control, Conscious, Unconscious), emotional valence (Positive, Negative), and test timepoint (Day 1, Day 2, Day 4).

For each combination of exposure condition, valence, and timepoint, the continuous efficacy variables, METEOR scores, will be summarized using descriptive statistics. Specifically, the mean and standard deviation (SD) will be calculated to provide an overview of performance across the different treatment groups. To formally compare METEOR scores between groups, paired t-tests will be conducted at a 5% significance level.

## Primary Efficacy Analysis

The primary efficacy analysis will assess the effect of cue exposure conditions (Conscious, Unconscious, Control) on short-term memory suppression, measured by METEOR scores. This analysis will be conducted across the total image group (include all images) as well as within the negative and positive image subgroups focusing on data collected at day 1.

For the total image group, the analysis will test whether METEOR scores for images in the Conscious and Unconscious exposure conditions are lower than those in the Control condition. Similarly, separate analyses will be performed for the negative image group and positive image group to determine if the same pattern holds within these subgroups. The following hypotheses will be tested using one-tailed paired t-tests at a 5% significance level:

- Total Image Group: METEOR scores for the Conscious and Unconscious conditions will be lower than for the Control condition.
- Negative Image Group: METEOR scores for the Conscious and Unconscious conditions will be lower than for the Control condition.
- Positive Image Group: METEOR scores for the Conscious and Unconscious conditions will be lower than for the Control condition.

To support these comparisons, descriptive statistics (mean, standard deviation, t statistics, p-values) will be calculated for each combination of exposure condition (Conscious, Unconscious, Control) and valence (Positive, Negative). These statistics will provide a clear summary of the METEOR scores across conditions and groups. The results of the primary efficacy analysis, including both descriptive summaries and statistical tests, will be presented in accordance with Section 8 of this SAP.

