## Endpoints

(ICH E9; 2.2.2)

1. Primary Endpoint

- Endpoint: Short-term memory suppression (METEOR scores).
- Definition: Memory suppression will be assessed using METEOR scores, a measure of semantic similarity reflecting accurate and context-rich recall.
- Time Point: Day 1 (immediately post-intervention).
- Comparisons:
- Cue exposure conditions: Conscious vs Control, Unconscious vs Control.
- Subgroup analysis: Positive vs Negative emotional valence.
- Hypothesis:
- Total Image Group: Conscious < Control, Unconscious < Control (one-tailed t-test).
- Negative Image Group: Conscious < Control, Unconscious < Control (one-tailed t-test).
- Positive Image Group: Conscious < Control, Unconscious < Control (one-tailed t-test).

2. Secondary Endpoints

- Endpoint 1: Long-term memory suppression (METEOR scores over time).
- Definition: Assessment of METEOR scores on Day 2 (24 hours post-intervention) and Day 4 (72 hours post-intervention) to evaluate memory suppression persistence.
- Time Points: Day 1, Day 2, Day 4.
- Analysis: Repeated paired t-tests (Conscious vs Control, Unconscious vs Control).
- Endpoint 2: Group differences in memory performance trajectories.
- Definition: Evaluation of memory decline over time using Difference-in-Differences (DID) analysis, adjusted for covariates such as: feedback Cycle Times (duration of self-feedback process during the learning phase), and frequency of Image Repetition (number of image viewings during the learning phase).
- Purpose: To supplement time-specific t-test comparisons and better understand group differences in forgetting trajectories.
- Endpoint 3: Emotional valence-based comparisons.
- Definition: Paired two-tailed t-tests comparing METEOR scores across valence conditions at each time point:
- Negative Treatment vs Positive Treatment
- Negative Conscious vs Positive Conscious.
- Negative Unconscious vs Positive Unconscious.
- Negative Conscious vs Positive Unconscious.
- Negative Unconscious vs Positive Conscious.

3. Exploratory Endpoints

- Endpoint: EEG-based neural activity analysis.
- Definition: Neural activity will be compared across cue exposure conditions and emotional valence groups using EEG power spectrum density.
- Frequency Bands: Alpha, beta, theta, delta, and gamma.
- Comparisons:
- Cue Exposure: Conscious vs Unconscious phases.
- Emotional Valence: Negative vs Positive image groups.
- Statistical Method: Two-tailed Wilcoxon signed-rank test for paired comparisons.

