## Secondary Efficacy Analyses

The secondary efficacy analyses will extend the evaluation of short-term memory suppression and further explore long-term effects, subgroup differences, and comparisons across emotional valence.

1. Long-Term Memory Suppression Analysis

The primary endpoint analysis conducted on Day 1 will be repeated on Day 2 (24 hours post-gaming) and Day 4 (72 hours post-gaming). This will determine whether the suppression effects observed (Conscious < Control, Unconscious < Control) persist over time, indicating long-term memory suppression.

1. Time-Based Changes in Memory Performance

To assess how memory performance changes over time for each subgroup (control, treatment, conscious, unconscious), a Difference-in-Difference (DID) analysis will be conducted. This analysis will be adjusted for the following covariates:

- Total duration of the self-feedback process during the Learning phase.
- Repetition frequency of each image during the Learning phase.

1. Emotional Valence Comparisons

To examine the differences between negative and positive emotional valence at each timepoint (Day 1, Day 2, Day 4), paired two-tailed t-tests will be performed. The comparisons will include:

- Negative Treatment vs Positive Treatment
- Negative Conscious vs Positive Conscious
- Negative Unconscious vs Positive Unconscious
- Negative Conscious vs Positive Unconscious
- Negative Unconscious vs Positive Conscious

These analyses will evaluate whether emotional valence influences memory suppression and whether differences between groups change over time.

To support these comparisons, descriptive statistics (mean, standard deviation, t statistics, coefficient estimates, p-values) will be calculated. The summary statistics and results for the secondary efficacy analyses will be produced in accordance with Section 8 of this SAP.

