# Listing of Tables, Listings and Figures

| **Table Title** | **Number** | **Population** | **Endpoint** | **Time Points or how to conglomerate** | **Covariates or Subgroups** | **Summary Statistics** | **Formal Analysis** | **Foot Notes** | |  |
| --- | --- | --- | --- | --- | --- | --- | --- | --- | --- | --- |
| Disposition | 1 | NA | Disposition | enroll-day4 | Treatment | count | NA |  | |  |
| Summary of Demographic Variable | 2 | Full Analysis | Age | Baseline | Treatment | n, mean, SD | NA |  | |  |
|  |  |  | Gender | Baseline | Treatment | p% (x/n) | NA |  | |  |
|  |  |  | Corrected Vision | Baseline | Treatment | n, mean, SD | NA |  | |  |
| Summary of scores (METEOR, Gist) | 3.1 | Full Analysis | METEOR scores | Day1 | Full(Treatment, Conscious, Unconscious), Negative(Treatment, Conscious, Unconscious), Positive(Treatment, Conscious, Unconscious) | n, mean, SD | NA |  | |  |
|  |  | Full Analysis | Gist scores | Day1 | As above | n, mean, SD | NA |  | |  |
|  | 3.2 | Full Analysis | METEOR scores | Day2 | As above | n, mean, SD | NA |  | |  |
|  |  | Full Analysis | Gist scores | Day2 | As above | n, mean, SD | NA |  | |  |
|  | 3.3 | Full Analysis | METEOR scores | Day4 | As above | n, mean, SD | NA |  | |  |
|  |  | Full Analysis | Gist scores | Day4 | As above | n, mean, SD | NA |  | |  |
| ShIF in short-term (paired t test) | 4.1 | Full Analysis | METEOR scores | Day1 | As above | n, mean, t statistics, p | NA |  | |  |
|  |  | Full Analysis | Gist scores | Day1 | As above | n, mean, t statistics, p | NA | | |  |
| ShIF in long-term (paired t test) | 4.2 | Full Analysis | METEOR scores | Day2-Day4 | As above | n, mean, t statistics, p | NA | | |  |
|  |  | Full Analysis | Gist scores | Day2-Day4 | As above | n, mean, t statistics, p | NA | | |  |
| DID analysis | 5.1 | Full Analysis | METEOR scores | Day1-Day2, Day2-Day4 | As above | Estimate, standard error, p | NA | |  |  |
|  | 5.2 | Full Analysis | Gist scores | Day1-Day2, Day2-Day4 | As above | Estimate, standard error, p | NA | |  |  |
| The difference in the Power Spectrum Density between “conscious and unconscious” | 6.1 | Full Analysis | PSD values | Day1 | Comparison (Conscious - Unconscious) | PSD, W statistics, p | NA | |  |  |
| The difference in the Power Spectrum Density between “positive and negative” | 6.1 | Full Analysis | PSD values | Day1 | Comparison (Positive - Negative) | PSD, W statistics, p | NA | |  |  |

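### Six one-tailed METEOR comparisons on Day 1 are all primary at 5% each, with no multiplicity control and no rule for which must succeed

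*SAP*

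**What the plan says.** Section 4.2 lists three pairs of hypotheses under the primary endpoint, METEOR on Day 1. The pair for all images reads "Total Image Group: Conscious < Control, Unconscious < Control (one-tailed t-test". The same two one-sided comparisons are then listed as separate hypotheses for the negative images and again for the positive images.

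Section 9.1 repeats them within the primary efficacy analysis and makes clear that the image sets overlap: "This analysis will be conducted across the total image group (include all images) as well as within the negative and positive image subgroups". It sets the level for all of them together: "The following hypotheses will be tested using one-tailed paired t-tests at a 5% significance level". The introduction to Section 9 likewise gives 5% for paired t-tests on METEOR. No section names an adjustment, a hierarchy, a single key comparison or a success rule.

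Other sections widen the set of Day 1 tests without saying what status the additions have:

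- Section 4.2 lists Gist under no endpoint, yet the a priori hypothesis in Section 7.3 says that "participants will exhibit lower METEOR and Gist scores for images cued through conscious or unconscious exposure", with Control as the comparator.
- Table 4.1 in Section 16 reports t statistics and p-values on Day 1 for both METEOR and Gist. Its groupings are carried down from Table 3.1: "Full(Treatment, Conscious, Unconscious), Negative(Treatment, Conscious, Unconscious), Positive(Treatment, Conscious, Unconscious".

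Section 9.2 adds that "The primary endpoint analysis conducted on Day 1 will be repeated on Day 2" and on Day 4. Those repeats are labelled secondary.

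**The concern.** The SAP itself fixes both the hypothesis list and the level per test, so this is not a detail left to a protocol. With six primary tests at the full 5% and no success rule, one p-value below 0.05 in any image set, for either exposure condition, could be reported as success on the primary endpoint. The 5% would then describe each test but not the trial's primary claim. The choice of which result counts would also remain open until the results are known.

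**Working it through.** The SAP states no familywise error rate, effect size or power, so there is no figure of its own to reproduce.

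**Inputs from the SAP**
- Number of primary tests: 2 contrasts x 3 image sets = 6 (Sections 4.2 and 9.1).
- Level: 0.05 each, one-tailed, paired (Section 9.1).
- Shared Control in a within-subject design (Section 5.1). The total set contains the negative and positive images (Section 9.1).
- Planned N = 150 (Section 6), used for degrees of freedom and detectable effect.

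**Assumptions, because the SAP gives no values**
- Equal cell variances and independent errors across conditions. Two contrasts that share Control then correlate 1/(1+1) = 0.5.
- Total score = mean of the negative and positive scores. With between-valence correlation r, a total contrast correlates √((1+r)/2) with its negative or positive counterpart, which is 0.71 at r = 0.
- No true effect in any comparison, and success on any one test.

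**Step 1: outer benchmark.** If the six tests were independent, 1 − 0.95^6 = 26.5%. They are positively correlated, so the true rate is lower.

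**Step 2: six correlated tests.** Simulation of the six z-statistics (1,000,000 draws) gives the probability of at least one p < 0.05:

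| Between-valence correlation r | Any one of six |
|---|---|
| -0.3 | 20.2% |
| 0 | 18.7% |
| 0.3 | 16.9% |
| 0.6 | 14.9% |
| 0.9 | 11.9% |

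Simulated t-tests with n = 150 and r = 0 give 19.0%. At r = 0, making the Control variance a quarter of, or four times, that of the other cells gives 20.2% or 16.1%.

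**Step 3: total-image pair only.** The two contrasts correlate 0.5 whatever r is. The rate is 8.8% (1 − 0.95² = 9.75% if independent).

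**Step 4: both contrasts required.** If Conscious and Unconscious must both be significant within an image set, the chance that this happens in any of the three sets is about 3% at r = 0.

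**Step 5: candidate fixes under no effect.**
- Holm on the total-image pair: a false rejection needs the smaller p below 0.05/2 = 0.025. The rate is about 4.5%.
- Holm over six: the smallest p must be below 0.05/6 = 0.0083. The rate is about 4% at r = 0.
- Valence tests gated behind the total-image result but run at 5% each: if the effect exists only in negative images and opens the gate, the two null positive-image tests err at 8.8%.

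**Step 6: detectable effect** in SD of the paired difference, at an assumed 80% power: d ≈ (z₁₋α + 0.842)/√n.

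| One-sided level | n = 150 | n = 75 |
|---|---|---|
| 0.05 | (1.645 + 0.842)/12.25 = 0.203; t-based 0.204 | 2.487/8.66 = 0.287; t-based 0.290 |
| 0.025 | (1.960 + 0.842)/12.25 = 0.229; t-based 0.230 | 2.802/8.66 = 0.324; t-based 0.328 |
| 0.0083 | (2.394 + 0.842)/12.25 = 0.264; t-based 0.267 | 3.236/8.66 = 0.374; t-based 0.381 |

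The n = 75 column is shown because Sections 5.2 and 5.3 exclude feedback cycle times outside the interquartile range, which by definition holds about half of a sample. Section 8.2 keeps such participants in the Full Analysis Population, so the analysed number is itself unclear.

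**The case against.** **The valence sets are only subgroups, and a lead pair is implied.** Section 4.2 uses the word subgroup, and Section 9.1 takes the total images first, then asks whether the pattern recurs within each valence. That suggests an order but does not fix one, since all six hypotheses are listed together at 5%. Even if the valence sets are put aside, the remaining pair runs at 8.8%.

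**Both contrasts may have to succeed.** Section 9.1 words each hypothesis jointly for Conscious and Unconscious, and on that reading the error is about 3%. Section 7.3, with its or, points the other way, and Section 4.2 writes the two as separate inequalities. This objection stands in part: the 19% belongs to the any-one-of-six reading, and the defect is that the SAP does not choose between the readings.

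**A larger figure is tempting.** A reader might count 18 Day 1 tests in Table 4.1 (2 scores x 3 image sets x 3 groupings) and infer a primary error rate of about 31%. The SAP does not support that. Neither Section 4.2 nor Section 9.1 calls Gist or pooled Treatment primary. The count also treats a groupings column carried down from a descriptive table as a list of nine contrasts per score, and the formal-analysis column for that table says NA. The 31% further assumes a METEOR-Gist correlation of 0.5 and uncorrelated valences. Nor should Days 2 and 4 be added, because Sections 4.2 and 9.2 already make them secondary.

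**Conclusion.** The point holds for the six primary tests. As written, the plan allows a primary success to be claimed at a false-positive rate well above the 5% it states: about 19% if any one test suffices and the valence contrasts are uncorrelated, and about 12% to 20% over the between-valence correlations tried. These figures are not in the SAP. They rest on no true effect anywhere, equal variances and the any-one reading. The unstated position of Gist and pooled Treatment on Day 1 is a separate gap in labelling and adds nothing to the primary error rate. The success rule should be settled before results are seen, because the primary conclusion depends on which result counts.

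**What to change.** In Sections 4.2 and 9.1:

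1. Define the primary family as METEOR, Day 1, total image group, Conscious vs Control and Unconscious vs Control, tested with Holm at an overall one-sided 5%. State that the primary claim applies only to the contrast or contrasts that Holm rejects.
2. Label the negative and positive image tests supportive. If they are meant to be confirmatory, put all six tests under one procedure that controls the overall 5%, such as Holm over six. Do not run gated valence tests at 5% each.
3. In Section 7.3 and Table 4.1, state that Gist and pooled Treatment are supportive and, like the already secondary Days 2 and 4, cannot alone support the primary claim. Say whether Treatment is a tested contrast.

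The cost is wording plus some sensitivity. At an assumed 80% power, Holm on the pair raises the detectable effect from 0.204 to at most 0.230 SD with 150 analysed, or from 0.290 to at most 0.328 SD with 75. Holm over six would raise it to at most 0.267 SD with 150, or 0.381 SD with 75. No additional data are needed.
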